### Randomization

Following manager consent, and prior to the information session, each team will be numbered randomly, using a random number generator, and then listed in numeric order. Teams will then be randomized to either Group 1 (organizational-level strategies only) or Group 2 (organizational-level strategies plus activity tracker), across location strata (site A and B) and team size strata within site A (small/large) using a randomization website [56]. The randomization schedule will be created by a university staff member not involved in the study. A project staff member will then apply the randomization schedule to the list of teams. Neither project staff nor participants will be blinded to participants’ randomization condition.

### Organizational-Level Intervention

All participants will receive the organizational-support intervention elements, which are based on the *Stand Up Australia* intervention [57]. The key intervention message is ‘Stand Up, Sit Less, Move More’ [57], which encourages staff to interrupt sitting at least every 30 minutes with a change in posture; replace sitting with standing or moving (working toward having equal amounts of sitting and upright activities in the day); increase physical activity of any intensity level; and to make these changes across the whole day, both during and outside of work hours.

#### Information Booklet and Participant Feedback

All participants will receive a booklet from the workplace champion, developed by the research team and customized to Lendlease’s branding and corporate style requirements. The booklet will cover the study rationale (ie, evidence on prolonged sitting and detrimental health outcomes) and purpose; general guidelines on optimal workplace activity; behavior change strategies related to the key intervention messages; and general information about the study procedure and timeline. All participants will also receive a summary email from the workplace champion of the aggregate results from the baseline assessment regarding sitting, standing and stepping, as well as individual feedback on sitting, standing and stepping time after each of the assessment points (to be emailed individually by project staff; adapted from a previous study [39]).

#### Stand Up, Sit Less, Move More Emails

The workplace champion will create five emails in consultation with project staff (adapted from a previous study [58]). One email will be sent every 2 weeks during the initial 3-month intervention period. The emails will consist of a ‘tip of the week,’ a study update from the workplace champion, a quote from a participant and/or manager, and an infographic or a picture of Lendlease staff engaging in the ‘Stand Up, Sit Less, Move More’ message. Project staff will be included on the emails to enable tracking of email content for process evaluation. While the emails will cease after week 10, it is expected that team managers will continue to implement the strategies promoted in the emails with their team throughout the rest of the 12-month intervention period.

#### Executive Management Support

In addition to the staff, managers and senior managers participating in the trial, senior global executives (eg, Chief Executive Officer) will also take part in the baseline assessment and will receive the information booklet and ‘Stand Up, Sit Less, Move More’ emails. The participation of the global executives, which demonstrates visible support for the intervention, will be communicated to staff by the workplace champion.

### Activity Tracker

Participants in Group 2 will be given the LUMOback activity tracker in addition to the organizational-level strategies. The LUMOback is worn around the waist as a belt, collecting information, and providing real-time feedback on sitting, standing, stepping, breaks from sitting, posture, and sleep. The LUMOback assesses activity by inertial sensors, which collect data at a constant 25 Hz [59], and is controlled through a mobile app via a Bluetooth connection that can be used by both iPhone operating system and Android platforms. Up to 3 weeks of data can be collected by the LUMOback before it must be synced with the app, with data transferred between the LUMOback and the app at 600 bytes/second. In the app, participants can view graphs, averages, and goals related to their sitting, standing, stepping, sitting breaks, posture (represented by an avatar, see Figure 2), and sleep. The device can monitor behavior, track attainment of the wearer’s goals, and provide real-time feedback. Participants can use the app to select the LUMOback to vibrate when they are sitting or standing in a ‘poor’ lumbar posture as identified by pelvic tilt angle [59], and to send a push notification to their mobile phone when they have been sitting too long. Vibrations can be chosen to be more or less intense, more or less exact about posture, or turned off; sitting notifications can be selected to range in time between 15 minutes and 2 hours of sitting, or turned off. The app also contains many learning videos about maintaining a good posture.

The LUMOback shows strong correlations and good agreement, in free-living conditions, with measures from the activPAL activity monitor in total time spent sitting (*R*
^2^=0.89 [60]; mean absolute percent error (MAPE)=9.5% [61]), standing (*R*
^2^=0.86 [60]), and number of steps (MAPE=0.4%, intraclass correlation coefficient (ICC)=0.99 [62]). In laboratory conditions, the LUMOback shows excellent agreement in step counts when tested against the Optogait treadmill test (MAPE=0.2%, ICC=0.99 [62]).

A LUMOback and a four-page instruction booklet that covers an introduction to the device, set-up instructions, and frequently asked questions will be distributed to Group 2 participants by the workplace champion following baseline assessments. On receipt of the device, participants will be asked to download the free app and sync the LUMOback with their phone. Participants will be asked to use their work email to set up their device as this will later be used to request the data from the company LUMO Bodytech. Participants can wear the device as much or as little as they like and their self-directed usage will be tracked. However, participants will be instructed by project staff to wear their LUMOback during the 3-month assessment period both to gather validity data and to estimate the intervention effectiveness while wearing the LUMOback. Participants will be allowed to keep the LUMOback.

**Figure 2 figure2:**
[figure not shown]
Representation of the LUMOback avatar while seated in a good posture.

### Data Collection

Data collection will occur at baseline, 3, and 12 months, and has been approved by the organization to occur during work hours. At each assessment, participants will be asked to wear an activPAL3 activity monitor continuously (24 hours/day) for 7 days, and to complete a concurrent electronic work and sleep diary. They will also be emailed a link to a Web-based questionnaire, using LimeService [63] covering demographic information (baseline assessment only), health- and work-related information (all assessments), and feasibility and acceptability (3- and 12-month assessments). Height and weight will be measured by a trained Lendlease staff member (site A) or project staff member (site B) during a face-to-face baseline assessment session that is expected to take approximately 15 minutes.

Individual qualitative interviews on the feasibility and acceptability of both of the interventions will occur following the 3-month assessment via telephone. Focus groups covering the long-term feasibility and acceptability of the interventions will be conducted as part of the 12-month assessment. Project staff will request LUMOback usage data from Lumo Bodytech every 2 weeks during the initial 3-month intervention period and then periodically throughout the rest of the study.

### Measures

An overview of the study feasibility, acceptability, and effectiveness outcome measures is provided in Table 1. In addition, a range of measures covering demographics, job, and health characteristics, psychosocial variables and technology confidence will also be collected.

#### Feasibility

Feasibility information will be examined in terms of participation, retention rates, and intervention delivery indicators, including the number of emails received (for the organizational intervention) and the degree of usage of the LUMOback activity tracker and app (assessed from the device and self-report). Ease of LUMOback data download and amount of lost or missing LUMOback data will also be evaluated. Table 1 displays an overview of the feasibility indicators and Multimedia Appendix 1 contains the questionnaire items created for the study.

The LUMOback data will be used to determine number of days, hours, and peak levels of usage. The data is expressed as a percentage of a 5-minute window spent in each activity type (sitting and standing in a good or bad posture, lying, sitting in a car, walking, and running), and step counts, calorie counts, and not worn/charging. No data is recorded over periods the device self-registers as off.

Telephone interviews and focus groups will be used to further evaluate both organizational support and LUMOback intervention strategies. Telephone interviews will identify: strategies implemented by the managers and organization; key facilitators and barriers of the intervention (including those specific to the LUMOback); and, any organizational culture changes that occurred (see Multimedia Appendix 2 for questions). Focus groups will discuss the impact of the interventions on the workplace culture and environment, long-term barriers and facilitators of the intervention strategies, and will identify any other key themes (see Multimedia Appendix 3).

#### Acceptability

Participants will be asked via questionnaire to rate how useful the emails and tips were, their satisfaction with the emails and information, and if they had experienced any discomfort or injury as a result of their study participation. Participants who indicate they have used a LUMOback device will also be asked to rate their comfort, ease of use, and perceived usefulness of the LUMOback (see Multimedia Appendix 1 for full list of questionnaire items). Participants who indicate they were given a LUMOback (whether they wore it or not) will also be asked would they recommend the LUMOback to a friend, how likely they were to use the LUMOback in the next 6 months, did they have any adverse experiences from using the LUMOback, and if they had any comments about the LUMOback or app. A shorter questionnaire at 12-month follow-up (to reduce participant burden and maintain compliance) will collect information relating to long-term LUMOback usage, adverse experiences, and comments. Telephone interviews and focus groups will also assess the acceptability of both interventions over the short and long-term (see Multimedia Appendices 2 and for questions).

#### Effectiveness

##### Activity Outcomes

The activPAL3 activity monitor will be used to measure the primary and secondary activity outcomes. The activPAL is a small device worn on the thigh (53×35×7 mm; 15 g). It has excellent interdevice reliability (ICC=0.79-0.99 [64]). It shows excellent validity relative to direct observation in measuring sitting/lying, hereafter termed ‘sitting,’ standing, and stepping, and for alterations between sitting and upright posture [64-66]. The activPAL has also shown responsiveness to change in sitting [66]. Correlations with direct observation of total time spent sitting, standing, and stepping, and total number of postural transitions are close to 1, mean differences reported are small and nonsignificant (eg, sitting and breaks measures all <2% bias) [65]. The agreement with direct observation of activity classification (sitting, standing, or stepping) moment by moment is also excellent (eg, 98.5% correct in a controlled setting, 93.6% correct during activities of daily living) [64]. Also, participants cannot extract activity data (real-time or otherwise) from the activPAL3, limiting reactivity.

The primary activity outcomes are time spent sitting at work and time spent sitting overall (ie, across all waking hours on work and nonwork days). The other activity outcomes relating to the ‘Stand Up, Sit Less, Move More’ message are listed in Table 1. In line with the exploratory nature of the pilot study, a range of other sedentary and physical activity measures (eg, usual sitting bout duration, number of steps) will be assessed and reported in addition to the study outcomes.

##### Health Outcomes

Physical and mental health-related quality of life [67] will be measured by the Short Form (SF)-12 version 1 at each assessment. The SF-12 correlates highly with the SF-36 (*r*=0.95 and 0.97) and has good test-retest scores (*r*=0.89 and 0.76) for the physical and mental components respectively [67]. Overall stress will be measured at each assessment by one item from the Health and Work Questionnaire [68].

##### Work Outcomes

Work-related outcomes will be measured via questionnaire at all assessments. These are work performance [69] and two measures from the Health and Work Questionnaire [68]: work satisfaction (four items, with α for internal consistency=0.84), and job control (one item).

**Table 1 table1:** Overview of study outcomes.

Measurement tools	Outcomes
Feasibility
Organizational support questionnaire items	Number of emails received
	What participants did with email (eg, read then delete)
	Perceived level of support to ‘Stand Up, Sit Less and Move More’ from (1) organization, (2) main manager, and (3) colleagues
LUMOback questionnaire items	Ever used (eg, yes, given but never used, no)
	Date of first use
	Setting of use (eg, workplace)
	Frequency of recalibration, app checking, goal checking, vibration and sitting alerts
LUMOback data	Days of usage
	Hours of usage/day
	Peak levels of usage
	Ease of data download
	Amount of missing data
Telephone interviews	Strategies implemented by manager and organization, organizational culture change, key elements of intervention, barriers of wearing the LUMOback at work and at home
Focus groups	Long term sustainability of changes, barriers and facilitators, key themes
Acceptability
Organizational support questionnaire items	Usefulness of emails and tips
	Satisfaction with emails and information received
	Adverse experiences from program in general
LUMOback questionnaire items	Comfort of LUMOback
	Ease of set up of LUMOback and app, navigating app, calibrating LUMOback
	Usefulness of LUMOback and app
	Likelihood of using LUMOback in next 6 months, adverse experiences from LUMOback, comments about the LUMOback
Telephone interviews	Acceptability of program, acceptability of the LUMOback
Focus groups	Acceptability of program, acceptability of long-term LUMOback wear
Effectiveness
Activity
activPAL	Stand up: standing time at work and overall
	Sit less: sitting time at work and overall (primary effectiveness outcomes); prolonged (>=30 mins) sitting time at work and overall
	Move more: stepping time at work and overall
Health
SF-12 v1	Physical and Mental health-related quality of life	
Health and Work Questionnaire	Overall stress
Work
Work performance rating scale	Work performance
Health and Work Questionnaire	Work satisfaction, job control

#### Demographics and Job Characteristics

Height and weight will be measured with shoes removed using a stadiometer (to the nearest 0.1 cm) and calibrated electronic scales (to the nearest 0.1 kg) at baseline only. Similarly, participants will be asked at baseline only their age, gender, Aboriginal or Torres Strait Islander status, highest level of education completed, and length of time at the workplace. Pregnancy status will be measured at 3- and 12-month follow-ups only, while current smoking status and smoking while at work will be measured at each assessment.

Full-time equivalence, job category, and percent of work time spent at desk, away from desk, and outside the workplace [58] will be measured at all assessments. Frequency and duration of working with colleagues [58] will be assessed at baseline and 3-month follow-up only. At 3- and 12-month follow-ups, workplace location will be assessed to account for any office relocations. Data on team location and team size will be collected by project staff at baseline.

#### Other Measures

Several additional individual, work, health, and intervention factors will be assessed to explore whether they predict changes in sitting and activity, and for consideration as potential confounders for relative effectiveness. The additional individual factors to be assessed include: confidence with technology and use of any other apps or wearable devices to help increase activity (see Multimedia Appendix 1), as well as psychosocial measures such as preference for sitting and standing at work, and knowledge of the health impacts of sitting [58]. These psychosocial variables have been derived from previous *Stand Up Australia* research [58], have moderate to good test-retest reliability (Spearman’s ρ=0.67-0.78) [38,58], and will be assessed at baseline and 3-month follow-up only. The additional health-related factors include perceived stress and musculoskeletal health. Specifically, at baseline and 3-month assessments only, perceived stress will be measured using the 4-item version of the Perceived Stress Scale [70]. The 4-item Perceived Stress Scale has good internal consistency (α=0.82) and correlates moderately with the Impact of Event Scale (*r*=0.58), 12-item Posttraumatic Stress-Arousal Scale (*r*=0.70), and the mental health component of the Medical outcomes Scale-SF 36 (*r*=0.70) [71]. Musculoskeletal health will be measured at each assessment using a modified 36-item version of the Nordic Musculoskeletal Questionnaire [72]. Modifications are that items will refer to the last 1 month (instead of 12 months) [73] and items will be added to assess how intense the pain was in the body part in the last 1 month (on a 0-9 scale, where 0 means no complaints and 9 means pain as bad as it can be) for those who indicated that they experienced a problem [74] (questions can be found in Multimedia Appendix 1). Work factors such as perception of supervisor relations (two items from the Health and Work Questionnaire [68], with α for internal consistency=0.85) will be measured at each assessment. Use of workplace strategies to sit less and move more (adapted from *Stand Up Australia* [58], full list of questions Multimedia Appendix 1) will be measured at all three assessments. Self-report activity will also be collected via the Occupational Sitting and Physical Activity Questionnaire (OSPAQ) [75]. Assessment of sitting using the OSPAQ correlates moderately with accelerometer (Actigraph GT1M) measured sedentary time (Spearman ρ=0.65) [75].

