### Statistical Analyses

Statistical analyses will be conducted in SPSS Statistics version ≥22 and Stata version ≥13 with statistical significance set at *P* <.05, two-tailed. Within-group changes in activity, work and health outcomes (continuous) will be assessed, using linear mixed-models that account for repeated measures and clustering, to determine the effectiveness of each intervention for these outcomes in the short- and long-term. To compare the relative effectiveness of the combined organizational-level and activity tracker intervention to organizational support alone, mixed-models will be used, adjusting for baseline values and potential confounders; these address both repeated measures and clustering. Confounders will initially be chosen a priori from the literature and retained in models if they are associated with the outcome at *P* <.2. Models will be checked for linearity, normality, and heteroscedasticity. Analyses will follow intention-to-treat principles. Per-protocol analyses will also be conducted to evaluate what the efficacy of the intervention is specifically for those who use the activity tracker, because activity tracker usage is self-directed. Assumptions regarding missing data will be checked and sensitivity analyses will be conducted to evaluate the impact of missing data on findings. Predictors of changes in activity will be evaluated by linear regression, adjusting for baseline values, and correcting for clustering. Predictors will be considered separately and also mutually adjusted. Characteristics of individuals will be considered as potential predictors including demographics (eg, age), psychosocial (eg, preference for sitting at work), health (eg, musculoskeletal problems) and work-related characteristics (eg, perception of relationship with supervisor), and engagement with the intervention (eg, LUMOback usage).

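### Factors arising from the intervention are eligible as confounders in the Group 2 versus Group 1 comparison, with no limit to pre-intervention values

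*Protocol article*

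**What the plan says.** Other Measures opens with a pool that spans individual, work and health factors as well as intervention factors, and one sentence gives it two purposes: "intervention factors will be assessed to explore whether they predict changes in sitting and activity, and for consideration as potential confounders for relative effectiveness". Relative effectiveness is the comparison of Group 2 (organizational strategies plus tracker) with Group 1 (organizational strategies alone).

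Several members of the pool are measured again after the intervention starts:
- The item on "Use of workplace strategies to sit less and move more" is one that "will be measured at all three assessments".
- The psychosocial items (preference for sitting or standing, knowledge) are ones that "will be assessed at baseline and 3-month follow-up only". Perceived stress follows the same schedule.
- Musculoskeletal health and supervisor relations are recorded at every assessment.
- For "use of any other apps or wearable devices to help increase activity", the article states no timing.

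Statistical Analyses adjusts the between-group mixed models for baseline values and for potential confounders. Its selection rule begins: "Confounders will initially be chosen a priori from the literature and retained in models". The condition for retention is an association with the outcome at P<.2. Predictors of change are handled in a separate linear regression, and engagement with the tracker is named only there.

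**The concern.** Predicting change and confounding a randomised contrast are different roles. Something that results from the intervention can be a sensible predictor of change, but it lies downstream of allocation and so cannot confound the comparison of the arms. A follow-up value of strategy use is the clearest case, because it records behaviour that the programme sets out to change.

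Conditioning on such a variable takes out the part of the tracker effect that passes through it. It can also bring in bias from common causes of that variable and sitting time. Screening on association with the outcome gives no protection, since a variable that carries the effect is associated with the outcome.

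This bears on the only effectiveness contrast protected by randomisation. Methodological Considerations acknowledges that, without an untreated control group, each intervention on its own can be judged only as a single-group before-and-after comparison.

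**Working it through.** **1. The plan's own figures (Sample Size and Table 2, sitting time).** Inputs: 75 per group, 30% attrition, design effect 1 + 0.1 × 4.83 = 1.483, SD 90, pre-post correlation 0.6.
- Effective n per group = 75 × 0.7 / 1.483 = 35.4.
- Within-group: SD of change = 90 × √(2 × (1 − 0.6)) = 80.5. Power for 45 minutes is 89.8% by the noncentral t (91.4% by the normal approximation), against 90% stated.
- Between-group: baseline-adjusted SD = 90 × √(1 − 0.6²) = 72, and SE = 72 × √(2/35.4) = 17.1. The minimum detectable difference is (1.96 + 0.84) × 17.1 = 47.9 minutes, or 53.6 with the change-score SD, against 50 stated.

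The sitting figures reproduce. The point disputes none of them.

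**2. Is there a limit to pre-intervention values?**
- Other Measures names intervention factors for the confounder role and sets no time point.
- In Statistical Analyses, baseline values and potential confounders are listed as separate items, so the former most naturally means the baseline of the outcome.
- Choosing candidates a priori from the literature governs how they are picked, not when they are measured.

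Neither section restricts the timing or excludes intervention factors.

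**3. What would happen if such a variable were entered.** The mediated share is an assumption, since the documents give none. Expected adjusted effect = (1 − share) × total effect. Total effect is set at 50 minutes, the stated minimum detectable difference; power is two-sided 5% with the SE held at 17.1.

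| Assumed share | Adjusted effect (min) | Power |
|---|---|---|
| 0% | 50 | 83% |
| 25% | 37.5 | 59% |
| 50% | 25 | 31% |
| 75% | 12.5 | 11% |

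Holding the SE fixed is a simplification.

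**4. Would the P<.2 screen keep it?** Completers number 150 × 0.7 = 105, and 105 / 1.48 gives an effective total of about 70. For a correlation r with the outcome, t = r × √68 / √(1 − r²), and the retention probability is about Φ(t − 1.28). The values of r are assumed.
- r = 0.15: t = 1.25, retained about 49% of the time.
- r = 0.25: t = 2.13, about 80%.
- r = 0.35: t = 3.08, about 96%.

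A simulation gave the same picture. It used 18 teams of 6, ICC 0.1, a true effect of −50 minutes, a mediator shifted 1 SD by the tracker (assumed), and ordinary least squares for the screen. At shares of 25%, 50% and 75% the mediator was kept in 70%, 99% and 100% of runs. The final estimates averaged −38.9, −25.1 and −12.2 minutes, against about −50 without it.

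**The case against.** The strongest reply is that no section says a follow-up value or an intervention factor will enter the between-group model. The re-measured items listed above also have a baseline value, and Questionnaire Procedure requires the baseline questionnaire before the intervention begins. Which time point supplies a covariate is often left to an SAP. That stands for the re-measured items. It does not cover the phrase naming intervention factors as candidate confounders, which is an express statement and not a silence.

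A reader might infer that the plan will adjust for LUMOback usage. The documents do not support this: usage is named only for the predictor regression, and under Activity Tracker the device goes to Group 2 alone, so it would hardly serve as a covariate between arms. A reader might also infer that the tracker comparison will be biased towards no effect. That is not supported either, because entry is only possible and the bias can run in either direction.

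Intervention factors are never itemised, so taking strategy use as the leading example is an inference. Choosing confounders a priori could in practice exclude mediators, but the text does not require it.

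Two practical objections also stand. A ban on all follow-up values would catch workplace location, which Demographics and Job Characteristics records at follow-up to account for office moves. And baseline is not pre-allocation: teams are randomised before the information session, tracker teams are told about the device on invitation, and nobody is blinded. Baseline self-reports could already reflect known allocation.

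**Conclusion.** The point holds as a defect of eligibility. The protocol admits factors arising from the intervention as candidate confounders of a randomised contrast, and sets no pre-intervention limit in the model that uses them. It does not commit to entering any.

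The possible loss is material: between a quarter and three quarters of a 50-minute effect over the assumed range of shares. Those shares, the correlations and the 1-SD mediator shift are illustrations, not properties of this trial. Relative effectiveness is a secondary aim of an exploratory pilot. The primary within-group analyses and Table 2 are unaffected. The wording should be corrected, but the point does not undermine the main aims.

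**What to change.** In Other Measures, split the opening sentence so that intervention factors serve only the predictor analyses, and individual, work and health factors may also be considered as confounders.

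In Statistical Analyses, add a sentence such as: *Confounders in the relative-effectiveness models will be limited to baseline values collected before the intervention begins.* Follow-up values stay available for the predictor regressions. Use of other apps or wearables would qualify only if a baseline value exists. Any use of follow-up workplace location to account for relocations should be a separate, labelled sensitivity analysis.

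The cost is a sentence in each section. No new data are needed and the sample size does not change. The fix does not remove the possibility that baseline self-reports were given with allocation known; that is better acknowledged as a limitation.
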